### Costs

We will estimate the cost of our four-component intervention, compare the costs of the intervention and control management strategies, and compute an incremental cost-effectiveness ratio. Costs will be estimated from the perspective of the French healthcare system, from randomisation to death or end of follow-up. Only direct costs will be counted. In each patient, all resources used will be recorded prospectively, using the same methodology in both groups. Resources used include the CGA [physician visits, medical interventions, and investigations], treatments [surgery, cytotoxic or targeted chemotherapy, radiotherapy, and supportive treatments (including recombinant human erythropoietin, anti-emetics, and colony-stimulating factors)], nutritional care [nutritional supplements and enteral nutrition], acute admissions for any reason, residence in a nursing home or rehabilitation unit, community care [physician visits and investigations during follow- up, number of physiotherapist sessions, number of home healthcare professional visits, and care provided at skilled nursing facilities]. The cost per resource unit will be taken from the cost lists established by the French statutory healthcare system. Differences in costs and differences in effectiveness on the primary endpoint will be used to estimate the incremental cost-effectiveness ratio. Costs will be reported as median [25th-75^th^ percentiles] and mean [SD] and compared using the Wilcoxon-Mann–Whitney test and parametric tests. Confidence intervals will be estimated by bootstrapping with 1000 re-samplings of the original dataset.

The significance level will be 5%. All tests will be two-tailed. Data will be analysed using Stata Software [College Station, TX, USA].

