## Methods/design

### Study design and setting

We are conducting an open-label, multicentre, parallel-group, randomised, controlled trial in patients aged 70 years or older and receiving standard care for HNSCC. One group receives a CGA-based multi-component intervention and the other does not [Figure 
1]. The primary endpoint is a composite criterion to be assessed after 6 months. Other endpoints such as OS and disease-free survival are assessed after 24 months. The patients are being recruited at 14 ENT/maxillo-facial surgery departments in 13 hospitals located in 9 cities in France [Paris, Créteil, Montfermeil, Villeneuve-Saint-Georges, Lille, Strasbourg, Nancy, Nantes, and Suresnes]. The protocol was approved by the appropriate ethics committee [CPP Ile-de-France I, Paris, France, approval April, the 20 April 2013;13213]. The trial is registered on ClinicalTrials.gov [NCT02025062].

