### Study intervention

The study intervention has four components.

(a) CGA before cancer treatment initiation, performed by a geriatrician [designated the ‘intervention geriatrician’ hereafter];

(b) participation of the intervention geriatrician in developing the cancer-treatment plan;

(c) standardised multidimensional geriatric therapeutic programme designed by the intervention geriatrician; and

(d) geriatric follow-up during cancer treatment and for 24 months after randomisation.

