#### (a) CGA

The CGA is performed by the intervention geriatrician, after randomisation and before the multidisciplinary meeting during which the cancer-treatment plan is established. The CGA consists in a detailed medical, psychological, and social assessment including a careful medical history and physical examination. In accordance with SIOG recommendations for elderly cancer patients, seven domains are assessed routinely: functional status, mobility and fall risk, nutritional status
[25], cognitive status, mood, co-morbidities and medications, and social environment. These domains are assessed using validated tests, questionnaires, scores, and/or scales [Table 
1]. Pain is also evaluated using a verbal numeric scale. The CGA is performed by a senior geriatrician, in some cases with help from a trained healthcare worker [usually a nurse working in the oncology and/or geriatric department].

**Table 1 T1:** Primary and secondary endpoints in the EGeSOR trial

**Endpoints**	**Time assessed**	**Description**
Primary endpoint	6 months after randomisation	Composite criterion including
		- death,
		- at least 2-point decrease in the Activities of Daily Living (ADL) score versus baseline
		- at least 10% decrease in body weight versus baseline
Secondary endpoints	6, 12, and 24 months after randomisation	- each component of the primary endpoint
		- progression-free survival
		- in-hospital death
		- unplanned admissions
		- post-surgery hospital stay length
		- discharge to home or nursing home
		- final cancer treatment plan (surgery, chemotherapy, targeted therapies, radiotherapy, and/or supportive care, alone or combined)
		- quality of life assessed by EORTC QLQ-C30 and specific module for head and neck cancer H&N35
		- treatment toxicities and/or complications: chemotherapy toxicities according to Classification Common Terminology Criteria for Adverse Events (CTCAE version 4.02)
		- cancer treatment feasibility
		- costs

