#### (d) Geriatric follow-up

The standardised geriatric follow-up provided by the intervention geriatrician, consists in a brief assessment of nutrition, mood, pain, functional status, the five above-listed co-morbidities, self-perceived health status, medication use, and implementation of the multidimensional geriatric therapeutic programme. The results of this standardised follow-up are used to make recommendations to the ENT physician, oncologist, radiotherapist and general practitioner.Follow-up includes closely spaced physical examinations for 1 to 6 months depending on the treatment modalities; Figure 
2 is an example for a surgically managed patient. After completion of the initial cancer treatment, the intervention geriatrician or nurse phones the patient every 3 months during the first 2 years after randomisation. If problems are identified during any of these phone calls, an appointment for a visit with the intervention geriatrician is scheduled.

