### Endpoints

Table 
2 shows the primary and secondary endpoints. The primary endpoint is a composite criterion evaluated 6 months after randomisation and including death, an at least 2-point decrease in the Activities of Daily Living [ADL] score
[27] versus baseline, and at least 10% weight loss versus baseline. A clinical research assistant blinded to the randomisation arm uses a standardised measurement guide to adjudicate the ADL score and weight. Weight is measured to the nearest 0.1 Kg using an electronic scale [Seca Model 876, Birmingham, United Kingdom]. Our decision to include functional and nutritional measures into the primary endpoint rests both on sound evidence that these measures influence treatment feasibility, patient survival, and quality of life; and on the potential for appropriate management to reverse functional impairments and weight loss.

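### The incremental cost-effectiveness ratio sets costs accrued over up to 24 months against an effect measured at 6 months, so its two terms cover different periods

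*Protocol article*

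**What the plan says.** The Costs section of the protocol article fixes both terms of the ratio.

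- **Numerator.** Direct costs are estimated from the perspective of the French healthcare system, "from randomisation to death or end of follow-up".
- **Denominator.** "Differences in costs and differences in effectiveness on the primary endpoint will be used to estimate the incremental cost-effectiveness ratio".

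The periods behind these terms are set elsewhere in the article.

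- **Effect.** The Endpoints section says: "The primary endpoint is a composite criterion evaluated 6 months after randomisation". The Abstract, Table 1 and the Discussion agree.
- **Follow-up.** Study design and setting says: "Other endpoints such as OS and disease-free survival are assessed after 24 months". The fourth intervention component is "geriatric follow-up during cancer treatment and for 24 months after randomisation". Under Geriatric follow-up, once initial cancer treatment is complete, the geriatrician or nurse "phones the patient every 3 months during the first 2 years after randomisation".
- **Planned assessments.** Table 1 lists the secondary endpoints, among them costs and each component of the primary endpoint, at "6, 12, and 24 months after randomisation".

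The Costs section also plans both median and mean costs, a Wilcoxon-Mann–Whitney test together with parametric tests, and bootstrap confidence intervals from 1000 re-samplings.

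**The concern.** A cost-effectiveness ratio can be read as a price per unit of benefit only if costs and benefits are counted over the same period. Here the numerator runs on after the denominator has closed.

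The arms can differ in cost after month 6. The intervention arm has scheduled calls, and visits if a call finds a problem; no such programme is described for controls. Admissions, nursing-home and rehabilitation stays and community care are also costed, and they continue in survivors in both arms. If the intervention improves survival, as the Background hypothesises, the additional survivors bring later costs, while survival gained after month 6 earns no credit. Conversely, any later saving lowers the ratio although the outcomes of that period are not counted.

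The Discussion concedes that the intervention is resource-intensive, and the Conclusion hopes to change how elderly patients with cancer are managed. A reader weighing that change would want a ratio with a clear horizon.

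**Working it through.** The article states no cost figure and no ratio, so there is nothing to reproduce. The check compares time windows and then uses assumed costs to show how the mismatch acts.

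**1. Windows**

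| Term | Source | Period |
|---|---|---|
| Cost difference | Costs; end of follow-up taken from Study design and setting, Study intervention, Table 1 and Geriatric follow-up | Month 0 to death or month 24 |
| Effect difference | Costs; timing from Endpoints and Table 1 | Month 0 to month 6 |

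The Costs section does not give the end of follow-up as a number. Twenty-four months is an inference, but the other sections support it and none gives a shorter period. For a patient alive at month 24, 24 − 6 = 18 months of cost have no matching effect. Nothing in the Costs section cuts the ratio's costs at month 6 or moves the effect to month 24.

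**2. What falls in the unmatched period**

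- Numerator: for a patient whose initial treatment is complete by month 6, about 18/3 = 6 routine calls in the intervention arm, any visits they trigger, and continuing care of survivors in both arms.
- Denominator: nothing. A death, functional decline or weight loss first occurring after month 6 is not counted. A death before month 6 is counted, because death is a component of the composite.

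**3. Sensitivity per unit of later cost**

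The planned effect under Sample size estimation is an absolute reduction of 0.10, from 30% in controls. Assume a mean cost difference of EUR 1,000 per randomised patient arising after month 6. The ratio then shifts by

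1,000 / 0.10 = EUR 10,000 per event avoided.

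The EUR 1,000 is an assumption chosen for scale.

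**4. Planned ratio against a matched 6-month ratio**

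Let a and b be the assumed mean incremental costs per randomised patient per month in months 0–6 and 6–24.

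- Planned: (6a + 18b) / 0.10
- Matched at 6 months: 6a / 0.10
- Planned divided by matched: (6a + 18b) / 6a = 1 + 3b/a

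| b/a | Planned ÷ matched |
|---|---|
| −0.5 | −0.5 (sign reverses) |
| 0 | 1.0 |
| 0.25 | 1.75 |
| 0.5 | 2.5 |
| 1.0 | 4.0 |

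The effect size cancels from this comparison. The two ratios agree only if the net cost difference after month 6 is zero. The article gives no information on b/a, so the table shows the mechanism and does not estimate the error.

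**The case against.** The strongest reply is that Table 1 schedules costs and each component of the composite at 6, 12 and 24 months, so either matched ratio can be computed, and that a condensed article may leave the economic details to a fuller document. The first part is right and makes the repair cheap. The second does not remove the point: the article states the cost window and names the effect, and an analysis plan that followed this text would inherit the mismatch. Choices such as restricted mean survival or weighting for censoring are a different matter. They are options for a fuller plan, and their absence is not an error.

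It can also be said that total follow-up cost per 6-month event avoided has a meaning, since it captures later costs or savings that follow from avoiding an early event. That stands in part. The quantity is not meaningless, but it leaves later benefit uncounted and should not be read as cost per event avoided over one horizon.

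Three stronger inferences are tempting and are not supported.

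- *That three quarters of the cost is unmatched.* The share 18/24 = 75% is calendar time for a patient alive at month 24. The geriatric assessment and treatment planning come before cancer treatment, the closely spaced examinations fall in the first 1 to 6 months, and routine geriatric contact after initial treatment is mainly a call every 3 months. Intervention cost may well be concentrated early.
- *That early deaths make the intervention look cheap.* A death before month 6 stops cost but counts as an event in the composite. Only later deaths go uncounted.
- *That the Wilcoxon test invalidates the cost comparison.* A rank test does not test the mean difference that forms the numerator, but means, parametric tests and bootstrap intervals are also planned, and nothing ties the rank test to the ratio. It can stay.

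**Conclusion.** The mismatch is real and is stated in the article: as written, costs over up to 24 months are set against an effect at 6 months. This rests on reading the end of follow-up as 24 months, which several sections support.

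Neither the size nor the direction of the distortion can be determined from the article. It is zero if the arms do not differ in cost after month 6, and it could inflate the ratio or reverse its sign otherwise. The euro figures and multiples above are illustrations on assumed costs.

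The consequence is confined to a secondary economic analysis. A reader might infer that it weakens the trial's main result; it does not, because the primary comparison and the sample size do not depend on the ratio. The correction is still worth making before analysis, because it is cheap and determines what the ratio means.

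**What to change.** State one horizon for both terms of each ratio in the Costs section.

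1. **Cost per composite event avoided:** mean cost difference with costs truncated at 6 months, over the difference in the 6-month composite.
2. **If a 24-month ratio is wanted:** mean cost difference to 24 months, over an effect measured to 24 months, for example survival or the composite rebuilt from its components at 24 months.

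Say also that the end of follow-up means 24 months after randomisation. Use the arithmetic mean difference and the bootstrap already planned for both ratios; the other planned cost comparisons can remain.

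The cost is a few sentences and a little extra analysis. No new data collection is needed, since resource use is recorded prospectively and Table 1 already schedules costs and the composite's components at both times. The small downside is that the 6-month ratio leaves out later costs, and covering them takes the second ratio.

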## Discussion

The EGeSOR trial aims to demonstrate that a multidimensional geriatric intervention based on an initial CGA, when added to standard care for HNSCC in elderly patients, significantly improves a 6-month composite endpoint of survival, functional status, and weight. The full picture of co-morbid conditions produced by the CGA may improve cancer treatment selection. Many elderly individuals have potentially fatal co-morbidities, which both compete with HNSCC as a cause of death and influence the risk/benefit ratio of cancer treatments. Moreover, the data on functional reserve provided by the CGA may help to predict the patient’s ability to tolerate specific cancer treatments. The personalised geriatric follow-up during cancer treatment, including adjustment of the treatments and management of the co-morbidities and iatrogenic complications, may increase the likelihood of cancer-treatment feasibility, improve quality of life, and decrease unplanned admissions and hospital stay length. Finally, the trial preparation phase strengthened the collaboration between ENT physicians and geriatricians, and we expect this beneficial effect to continue throughout the trial.

The study intervention consists of four components: the CGA performed by the intervention geriatrician at baseline, participation of the intervention geriatrician in developing the cancer treatment plan, a standardised multidimensional geriatric therapeutic programme, and geriatric follow-up for 24 months. The first two components have been proven to benefit treatment decisions
[23,33-35]. A Cochrane Collaboration meta-analysis showed that the last two components improved survival and maintenance at home in elderly patients with non-malignant diseases
[20]. The SIOG has recommended performing the CGA in vulnerable elderly patients with cancer
[21]. However, no previous studies evaluated the impact of the CGA in elderly patients with cancer.

The EGeSOR trial has several limitations. First, the CGA is time consuming and requires extensive involvement of geriatric teams, which may not be available in some centres. We visited each of the study centres to verify that the number of geriatricians was sufficient, and we considered reinforcing the geriatric team if necessary. Second, the primary endpoint is a composite criterion. However, demonstrating superiority of the study intervention on a single endpoint would have required such a large sample size as to compromise feasibility of the trial. Third, contamination bias may occur between the intervention and control groups, as each ENT physician manages patients in both groups. Conceivably, ENT physicians may apply knowledge acquired by managing intervention patients to their control patients, for instance by asking geriatricians for advice regarding vulnerable controls. Such contamination bias would diminish the size of the effect of the intervention. However, any contamination bias is probably limited, since modifications potentially introduced by ENT physicians in controls would have a very small effect compared to the full four-component intervention. Nevertheless, we are recording the number of times that advice from geriatricians is provided for control patients. Our study had several strengths. To our knowledge, it is the first randomised controlled trial evaluating the efficacy of the CGA in elderly cancer patients. We decreased the risk of selection bias by using randomisation with minimisation, the risk of evaluation bias by selecting objective clinical endpoints and using independent adjudication, and the risk of confusion bias by using randomisation with minimisation and a pre-specified multivariate analysis to correct for any baseline between-group imbalances. Finally, the standardised multidimensional geriatric therapeutic programme was designed in accordance with the most recent clinical recommendations and relied on validated international measurement tools.

## Conclusion

The CGA has been proven in several randomised trials and meta-analyses in the general geriatric population to improve survival, institutionalisation rates, and functional status. The EGeSOR trial is the first randomised trial of the CGA in elderly cancer patients. We expect to demonstrate a direct clinical benefit of the CGA on outcomes of elderly patients with HNSCC. If such a benefit is found, the results of the EGeSOR trial may change the healthcare management model for elderly patients with cancer.

## Abbreviations

ADL: Activities of daily living; CGA: Comprehensive geriatric assessment; ENT: Ear nose throat; HNSCC: Head and neck squamous cell carcinomas; ICER: Incremental cost-effectiveness ratio; OS: Overall survival; SIOG: International geriatric oncology society.
